### Treatment Planning

For particle therapy, patients will be immobilized using an individually manufactured head mask. For treatment planning, contrast-enhanced CT as well as MR-imaging will be performed for optimal target definition.

Patients included to the study will have received 48-52 Gy of photon RT applied to the resection cavity, area of contrast enhancement on T1-weighted MR-Imaging, T2-weighted hyperintensities including a safety margin of 2-3 cm.

Treatment planning for carbon ion and proton radiotherapy should be performed during photon radiotherapy about 1-2 weeks prior to the start of the carbon ion or proton boost.

Organs at risk such as the brain stem, optic nerves, chiasm and spinal chord will be contoured. Dose constraints of normal tissue will be respected according to Emami et al. [14]. The Gross Tumor Volume (GTV) will be defined for the proton or carbon ion boost as the area of contrast enhancement on T1-weighted MR-imaging; for the Clinical target Volume (CTV), a safety margin of 5 mm is added.

Amino-Acid-PET or SPECT-Examinations may be used in addition to contrast-enhanced MRI for target volume definition but are not mandatory.

Carbon ion RT planning is performed using the treatment planning software PT-Planning (Siemens, Erlangen, Germany) including biologic plan optimization. Biologically effective dose distributions will be calculated using the a/β ratio for GBM as well as for the endpoint late toxicity to the brain.

No interruptions >4 days between the end of photon radiotherapy and study treatment (carbon ion or proton boost) are allowed.

Patient positioning prior to particle therapy will be evaluated by comparison of x-rays to the DRRs. Set up deviations >3 mm will be corrected prior to radiotherapy.

### Dose Prescription Experimental (Carbon) Arm

The intensity-controlled rasterscan system will be used for beam application. Six fractions of a single dose of 3 Gy E up to a total dose of 18 Gy E will be prescribed to the maximum of the calculated dose distribution for the target volume (Boost). Treatment planning aims in the coverage of the target volume by the 90%-isodose line.

Dose specification is based on biologic equivalent dose because of the high relative biologic effectiveness (RBE) of carbon ions, which differs throughout the target volume due to its dependence on various factors. RBE will be calculated at each voxel throughout the target volumes and biological optimization will be performed. The dose prescription used is related to the isoeffective dose Gy E (Cobalt Gray equivalent) using daily fractions of 2 Gy and a weekly fractionation of 5 × 2 Gy.

### Dose Prescription Standard (Proton) Arm

The intensity-controlled rasterscan system will be used for proton beam application. Five fractions of a single dose of 2 Gy E up to a total dose of 10 Gy E will be prescribed to the maximum of the calculated dose distribution for the target volume (Boost). Treatment planning aims in the coverage of the target volume by the 90%-isodose line.

For proton beams, an RBE of about 1.1 can be considered. Therefore, the 10 Gy E applied with proton radiotherapy after treatment of 50 Gy with photons prior to study inclusion add up to the standard dose of 60 Gy used in conventional chemo-radiation with TMZ.

### Follow-up

The primary endpoint is overall survival at 12 months, therefore patients are followed within the trial protocol for a minimum 12 months after completion of study treatment. For the LPI, the final study visit will be 12 months after study treatment to assess the primary endpoint. All other patients will be followed on a regular basis as stated below until death or until 12 months after LPI.

After RT, patients are scheduled for follow-up visits every 2 months or as needed clinically including contrast-enhanced MRI as well as thorough clinical-neurological assessment.

The last patient included into the study will be followed 12 months after treatment. This is considered the final study visit. All other patients will be followed regularly as described in detail until death or until 12 months after LPI.

If death occurs <12 months or patients leave the study prior to12 months, they will be still included into the ITT population.

The overall duration of the trial is expected to be approximately 48 months. Recruitment of the patients is planned over a time period of 36 months, minimum duration of the follow-up phase will be 12 months. An interim analysis is planned after 50% of the expected events have occurred.

### Statistical calculations for trial sample size

The calculation of sample size for the CLEOPATRA trial is based on the analysis of the primary endpoint 'time to death for any reason during the follow-up phase of at least 12 months (starting with initial diagnosis)' using the logrank test to compare the survival curves of the experimental and the standard treatment. The specific assumptions and methods underlying this calculation are explained below.

#### 1. Recruitment period, follow-up duration and allocation ratio

The recruitment period will last 36 months with constant accrual. The minimum follow-up time (for the last patient included in the trial if no event occurs before) will be 12 months, the maximum follow-up time (for the first patient included in the trial if no event occurs before) will be 48 months. Patients will be randomized to the treatment groups with an equal allocation ratio of 1:1.

#### 2. Overall survival rate

Stupp et al. [2] investigated a study population very similar to the one expected in the CLEOPATRA trial. Hence, according to their results the one-year survival rate for the standard treatment is expected to be about 60%.

#### 3. Treatment effect size

The CLEOPATRA trial will be designed to detect an improvement of 20% (absolute) in survival rate after 12 months. The rationale behind this assumption is as follows: Carbon ion radiotherapy is characterized by a higher relative biological effectiveness (RBE) as compared to conventional photons or protons. Preclinical experiments on glioblastoma cell lines have shown that this RBE lies between 3 and 5, depending on the respective endpoint or cell line [9]. Therefore, the effect of carbon ion radiotherapy for the treatment of patients with primary glioblastoma is expected to be substantially higher than with conventional proton radiotherapy.

#### 4. Type I error rate and power

Time to death for any reason will be compared between the two treatment groups using a two-tailed logrank test stratified for RPA class at an overall type I error rate of 5%. The desired power is 90%. Sample size calculation is based on the unstratified logrank test. It can be expected that including the RPA class (which has a major prognostic impact on survival [2]) as a covariate will actually increase the power as compared to the unstratified test. For this reason, the sample size resulting from our calculations should assure the desired power of 90% under the assumptions made.

#### 5. Interim analysis

An interim analysis will be performed according to the stopping rule of O'Brien-Fleming published in 1979 after 50% of the expected events have been occurred [15].

#### 6. Methods used for sample size calculation

For sample size calculation, exponentially distributed survival times are assumed to calculate the hazard ratio under the alternative. Th*e *formulae proposed by Schoenfeld (which hold true under the less restrictive assumption of proportional hazards) were used [16,17]. Calculations were done using the software ADDPLAN 4.0 [18].

Using the assumptions enumerated above, the resulting total sample size yielding the necessary number of events is 150 patients (75 per treatment group). The expected total number of events under the null-hypothesis is then about 136, under the alternative-hypothesis it amounts to about 115. The total sample size of 150 patients will provide a power of 90,7% to detect a 20% (absolute) improvement in 12 months overall survival rate of the experimental treatment compared to the standard treatment. With this target sample size, CLEOPATRA will also have an adequate power to detect a smaller than anticipated treatment effect (more than 78% power to detect an improvement of 17% (absolute) in 12 months overall survival rate).

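### The expected event counts (136 and 115), and the power and interim figures tied to them, do not follow from the stated survival, accrual and follow-up assumptions, which give about 104 and 83 events at month 48

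*Protocol article*

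**What the plan says.** The protocol article lists its planning assumptions under the heading on sample size calculations and says that the results follow from them.

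- Standard arm (2. Overall survival rate): "the one-year survival rate for the standard treatment is expected to be about 60" per cent.
- Effect (3. Treatment effect size): the trial is "designed to detect an improvement of 20% (absolute) in survival rate after 12 months", that is, 60% to 80%.
- Distribution (6. Methods used for sample size calculation): "exponentially distributed survival times are assumed to calculate the hazard ratio under the alternative".
- Accrual (1. Recruitment period, follow-up duration and allocation ratio): "The recruitment period will last 36 months with constant accrual".
- Follow-up (same section): event-free patients are observed for between 12 months (last to enter) and 48 months (first to enter).
- Allocation (same section): 1:1.

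Section 6 then gives 150 patients and states: "The expected total number of events under the null-hypothesis is then about 136, under the alternative-hypothesis it amounts to about 115". It adds power of 90.7% for a 20-point improvement and more than 78% for 17 points. The Interim Analysis section takes half of the null count, 68 events, and expects it about 26 months after recruitment starts. The Confirmatory Analysis section sets one-sided levels of 0.26% at the interim and 2.4% at the end.

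**The concern.** If 60% of standard-arm patients are alive at one year and the last patient is followed for only 12 months, 136 deaths among 150 patients (91%) by month 48 is implausibly many. In a logrank trial the information is the number of events. The stated power, the interim trigger and the interim date all rest on these counts. If the counts do not belong to the stated survival rates, the reader cannot tell which hazard ratio the trial was sized for. Half of the expected events and 68 events also become two different interim triggers.

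**Working it through.** **Event probabilities on the stated inputs.** With hazard λ = −ln(S12)/12, uniform accrual over A = 36 months and minimum follow-up F = 12:

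P(event) = 1 − [exp(−Fλ) − exp(−(A+F)λ)] / (Aλ)

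No dropout is stated, and dropout would only lower the counts.

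- Standard: λ = 0.04257; P = 1 − (0.6 − 0.6⁴)/1.5325 = 0.693.
- Experimental: λ = 0.01860; P = 1 − (0.8 − 0.8⁴)/0.6694 = 0.417.

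**Event counts at month 48.**

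- Null: 150 × 0.693 = 104.0, against 136 stated. 136/104.0 = 1.31; 1 − 104.0/136 = 24% fewer.
- Alternative: 75 × (0.693 + 0.417) = 83.2, against 115 stated. 115/83.2 = 1.38; 1 − 83.2/115 = 28% fewer.

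If 115 is an average over early stopping, the comparable figure is d × (1 − p₁/2), where p₁ is the chance of crossing the boundary at a half-information interim. With d = 83.2 and p₁ = 0.451 this is about 64.

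**Other readings that keep 60% and 80% survival.**

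| Variant | Null | Alternative |
|---|---|---|
| Minimum follow-up 15 months | 109.5 | 88.4 |
| Minimum follow-up 24 months | 122.4 | 101.2 |
| Minimum follow-up 36 months | 133.4 | 113.7 |
| Every patient followed 48 months | 130.6 | 109.6 |

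The 36-month variant comes near but contradicts section 1. Replacing the 60% rate by a 14.6-month median gives 109 under the null. Reaching 136 with one common curve needs 12-month survival of about 33%.

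**Power.** HR = ln 0.8/ln 0.6 = 0.437. By Schoenfeld, power = Φ(|ln HR|·√d/2 − 1.96).

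- 20 points, d = 83.2: Φ(3.78 − 1.96) = 96.5%; 96.4% with the two-look boundaries. Stated: 90.7%.
- 17 points (77% survival, HR 0.512), d = 87.0: 87.8%; 87.6% with the two-look boundaries. Stated: more than 78%.
- The stated counts do not give the stated power either: at HR 0.437, 115 events give 99.3%, while 90.7% needs only about 63 events (71 by Freedman's formula).

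**Interim.** Half of 104 is 52 events, reached at about month 29 under the null. The stated 68 events are 68/104.0 = 65% of the null total and 68/83.2 = 82% of the alternative total. They arrive at about month 34 (null) or month 40 (alternative). At month 26 only about 43 (null) or 33 (alternative) events are expected.

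**An input set that does reproduce the plan.** Treat 60% and 80% as 12-month death rates, so survival is 40% versus 20% and HR = ln 0.4/ln 0.2 = 0.569.

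| Figure | Stated | Recomputed |
|---|---|---|
| Events | about 136 | 75 × (0.864 + 0.959) = 136.7 |
| Events under the alternative | about 115 | 136.7 × (1 − 0.321/2) = 114.8 |
| Power, 20 points | 90.7% | 90.7% |
| Power, 17 points (60% vs 77% dying) | more than 78% | 78.3% |
| Time of 68 events | about month 26 | month 25.5 |

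Here 136.7 is the two-arm total, or 136.3 after allowing for the rare early stop when there is no treatment difference. A common 40% survival curve in both arms would give 129.6. The 114.8 is a group-sequential average.

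**The case against.** The strongest defence is that the error does little harm. The final analysis is set by the calendar, 12 months after the last patient, and not by reaching 136 events, so the trial cannot stall. On the stated assumptions 150 patients give about 96% power, above the 90% target. Keeping the 0.26% and 2.4% levels with a look at 68 events gives an overall two-sided error of about 4.9% (68 of 104) or 4.8% (68 of 83). All of this stands.

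It is also fair to say that 115 may not be a month-48 count. In a group-sequential design, planning software may report a count averaged over early stopping, and the reproduction above suggests that it did. So 83 is not necessarily a direct replacement for 115. On that reading the gap is wider (64 against 115), so the mismatch remains.

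A reader might go further and infer that the trial is underpowered, that its error rate is inflated, or that survival and death rates were certainly swapped. The documents support none of these. The first two fail on the figures just given. The third is an inference from the pattern of matches; the protocol article does not say how the rates were entered.

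**Conclusion.** The stated event counts are wrong as written. On the protocol's own inputs the month-48 counts are about 104 and 83, not 136 and 115; no other section rescues the stated values. Both power figures, the 68-event trigger and its date fail on the same inputs. The practical damage is misreported power, an early-efficacy look that comes 8 to 14 months later than planned (month 34 or 40 instead of 26), and doubt about whether the design hazard ratio is 0.437 or 0.569. These conclusions assume exponential survival, uniform accrual and no dropout. That the 90% power target is met further assumes the full 20-point effect on a 60% baseline.

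**What to change.** Confirm the intended 12-month survival rates and re-run the whole calculation from them, rather than replacing two counts. Then restate together:

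- the expected events under each hypothesis, saying whether the figure under the alternative allows for early stopping;
- the power for 20 and for 17 points;
- the interim trigger and its expected date. If 60% survival is intended, these are about 52 events at about month 29 under the null.

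If other rates were intended, correct sections 2 and 3 (Overall survival rate; Treatment effect size) instead. The cost is one run of the planning software and a text correction. On the stated assumptions no extra patients are needed.

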### Statistical Methods

#### Confirmatory Analysis

A confirmatory analysis with characteristics common for studies designed for the proof of efficacy (two-sided test problem with significance level 5%) is implemented in this Phase II study in order to be able to show superiority of the experimental treatment as compared to the standard treatment in case of a significant result. Confirmatory analysis for the primary endpoint 'time to death for any reason during the follow-up phase of at least 12 months (starting with initial diagnosis)' is based on the full analysis set which is defined according to the intention-to-treat principle and includes all randomized patients. The null-hypothesis of equal survival curves for the two treatment groups is tested by applying the two-sided logrank test stratified by *RPA class. The overall type I error rate is 5%. A g*roup-sequential design is applied with one interim analysis after half of the expected number of events has occurred. The stopping rule is according to [15]: The one-sided critical level in the interim analysis is given by 0.26%, and in the final analysis it is given by 2.4%; the null-hypothesis can be rejected, if the smaller of the two one-sided p-values falls below one of these boundaries. Withdrawals, lost of follow-ups and patients who are still alive by the end of the follow-up phase are treated as censored observations. The censoring date is given by the last known date at which the patient is still alive. The survival curves will be estimated using the Kaplan-Meier product-limit method, and the corresponding confidence intervals will be calculated using Greenwood's formula [19].

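### The printed power, event counts and interim timing do not follow from the stated 60% and 80% survival rates: 150 patients would give about 96% power, not 90.7%

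*Protocol article*

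**What the plan says.** The inputs are spread over the numbered items under Statistical calculations for trial sample size in the protocol article.

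- **Item 1:** 36 months' constant accrual, follow-up between 12 and 48 months, 1:1 allocation.
- **Item 2:** expected one-year survival on standard treatment of about 60%.
- **Item 3:** an absolute gain of 20 points in 12-month survival.
- **Item 4:** two-sided 5% and a 90% power target. It adds that "Sample size calculation is based on the unstratified logrank test" and that "the sample size resulting from our calculations should assure the desired power of 90% under the assumptions made".
- **Item 6:** exponential survival and Schoenfeld's formulae, from which "the resulting total sample size yielding the necessary number of events is 150 patients (75 per treatment group"). Expected deaths are given as about 136 under the null and 115 under the alternative. On power: "The total sample size of 150 patients will provide a power of 90,7% to detect a 20% (absolute) improvement in 12 months overall survival rate", and also "more than 78% power to detect an improvement of 17% (absolute) in 12 months overall survival rate".

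Confirmatory Analysis fixes the boundary: "The one-sided critical level in the interim analysis is given by 0.26%, and in the final analysis it is given by 2.4" per cent. Interim Analysis, under Statistical Methods, places the look at half the events expected under the null, namely 68 deaths at about month 26. No dropout rate is given.

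**The concern.** Every input that the calculation needs is printed, so the result can be checked, and it does not reproduce. A 60% versus 80% split in 12-month survival is a large effect (hazard ratio 0.437), and 90% power for it takes far fewer deaths than the article expects. Conversely, at 60% and 80% survival, 150 patients followed to month 48 cannot be expected to produce 136 or 115 deaths.

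Two things are at stake. A reader of a null result would judge the trial's sensitivity from power figures that are 6 to 10 points too low. And the same calculation supplies the interim trigger and its calendar date, on which the group-sequential plan and trial logistics rest.

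**Working it through.** **Inputs (all from the article).** 12-month survival 60% versus 80% (or 77%); accrual 36 months, cut-off at month 48; 75 patients per arm; one-sided critical levels 0.26% and 2.4%, i.e. critical values of about 2.80 and 1.977; interim at half the events. Assumed here: no dropout, and survival counted from entry.

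**Formulae.**
- Monthly hazard h = −ln(S12)/12.
- P(death by month 48) = 1 − [exp(−12h) − exp(−48h)]/(36h).
- With d deaths and 1:1 allocation, the final logrank statistic has mean θ = |ln HR|·√d/2; the interim statistic has mean θ/√2 and correlation √0.5 with the final one. Power = 1 − P(Z1 < 2.80 and Z2 < 1.977).

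**Step 1. The printed figures, with 60% and 80% entered as death rates** (survival 40% versus 20%; for 17 points, 40% versus 23%).
- HR = ln 0.2/ln 0.4 = 1.756. P(death) = 0.864 and 0.959. Deaths at month 48 = 75 × (0.864 + 0.959) = 136.7.
- θ = 0.563 × √136.7/2 = 3.29; power 90.7%.
- Chance of crossing at the interim under the alternative = 0.320, so expected deaths = 136.7 × (1 − 0.320/2) = 114.8. Under the null the chance is 2 × 0.0026, giving 136.7 × (1 − 0.0026) = 136.3.
- Half of 136.7 is about 68, reached at month 25.5.
- 17 points: HR 1.604, 135.9 deaths, power 78.3%.

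| Quantity | Printed | Rates entered as deaths | Rates entered as survival (as stated) |
|---|---|---|---|
| Deaths, null | about 136 | 136.3 | 104 |
| Deaths, alternative | about 115 | 114.8 (with interim stop) | 83 by month 48 |
| Power, 20 points | 90.7% | 90.7% | 96.5% |
| Power, 17 points | more than 78% | 78.3% | 87.6% |
| N | 150 | about 150 (for 90.7%) | about 111 (for 90%) |
| 68 deaths at | about month 26 | month 25.5 | month 34 (null), 40 (alternative) |

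**Step 2. The inputs as stated.**
- h = 0.0426 and 0.0186; HR = ln 0.8/ln 0.6 = 0.437.
- P(death), control = 1 − (0.6 − 0.1296)/(36 × 0.0426) = 0.693. Experimental = 1 − (0.8 − 0.4096)/(36 × 0.0186) = 0.417.
- Deaths: null 150 × 0.693 = 104; alternative 75 × (0.693 + 0.417) = 83.2.
- θ = 0.828 × √83.2/2 = 3.78; power 96.5%. Simulated logrank trials with both looks gave 96.3%.
- 17 points: HR = ln 0.77/ln 0.6 = 0.512; deaths 75 × (0.693 + 0.466) = 87; power 87.6% (simulation 86.4%).

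**Step 3. Size for 90% power.** Solving the power equation at HR 0.437 gives 61.7 deaths. The average death probability is (0.693 + 0.417)/2 = 0.555, so N = 61.7/0.555 = 111. Simulation reached 90.0% at N = 114.

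**Step 4. The interim.** 68/104 = 65% and 68/83.2 = 82% of the deaths reachable by month 48, not 50%. Reaching 136 deaths would take about 76 months even under the null.

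**Step 5. Other readings tried with the stated survival rates, for 20 points.** Freedman's formula gives 94.6% (85.1% for 17 points); deaths within 12 months only, 79.0%; a two-proportion test, 76.7%. None gives 90.7%.

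**The case against.** The best defence is that the printed numbers are not a jumble. They agree with each other, and the disagreement is only with the survival rates in items 2 and 3. That is right, and it rules out three stronger readings that a reader might reach.

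- *The printed powers belong to a trial with only 63 to 67 deaths.* At the stated hazard ratios, 90.7% and 78% do correspond to about 63 and 67 deaths. But that reading explains the two powers and nothing else, whereas the death-rate reading recovers the whole set.
- *The printed 115 deaths imply 99.3% power.* This treats 115 as the final-analysis count. It matches the average number of deaths allowing for an interim stop (114.8), so it does not belong in the power formula.
- *The late interim inflates the type I error.* Applying the printed critical levels at 65% or 82% of the information gives an overall two-sided error of about 4.9% or 4.8%, so it does not.

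A second defence is unstated dropout. At an assumed 20% annual loss, power is 91.9% for 20 points and 79.4% for 17, and a slightly higher rate would come close to both printed powers. But at 20% to 30% annual loss the deaths expected under the null fall to about 84 to 75, further from 136. Dropout does not explain the set, and a condensed article's silence on it is no fault.

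The consequence is also limited. The error runs in the safe direction, and neither the test nor the estimate is affected.

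**Conclusion.** The power, sample-size and event figures in item 6 do not follow from items 1 to 4. Under the stated inputs, 150 patients give about 96% power for 20 points (printed 90.7%) and about 87% for 17 points (printed just over 78%), with about 104 deaths under the null and 83 under the alternative. About 62 deaths, or roughly 111 to 114 patients by Schoenfeld's formula, would give 90%.

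This does not make the trial underpowered for its target: the 90% assurance in item 4 is met with room to spare. What is wrong is the stated sensitivity, the event counts, and the size and date of the interim. These are one defect, because a single calculation produced them all.

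That survival rates were entered as death rates is an inference from the joint match; the article does not say so. The figures rest on exponential survival from entry, uniform accrual, a month-48 cut-off and no dropout. With an assumed 10% annual loss, power would be 94.5% and 83.8%.

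**What to change.** 1. Check which rates were entered in the sample-size software, and rerun the calculation with 60% and 80% (and 77%) as survival rates.
2. Keep 150 patients. In item 6, restate power as about 96% for 20 points and about 87% for 17 points, with about 104 (null) and 83 (alternative) deaths by month 48. State that 90% power needs about 62 deaths, and stop presenting 150 as the number that the 90% requirement yields.
3. In Interim Analysis, recalculate the trigger and date from the same run. By the article's own rule, half of the deaths expected under the null is 104/2 = 52, not 68. Moving the look from 68 to 52 deaths changes power by less than 0.1 point.
4. If some other input produced 90.7%, state it. Do not describe the surplus over 111 to 114 as a reserve for losses unless one was planned; nothing in the article says so.

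Cost: one rerun, corrections to two paragraphs, and a new interim trigger fixed before any interim data are seen. Enrolment, the test and the critical levels stay as they are.
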